### Walk with Me intervention

The 12-week intervention begins with a face-to-face meeting between the peer mentor, the participant and a member of the research team whose role is to facilitate initial discussions. At this introductory meeting, there is a discussion of the peer mentor’s role and the main behaviour change components of the intervention are described (goal setting, reviewing and setting behavioural goals, problem-solving). The participant is given a pedometer to keep (Yamax SW-200, Yamax Corp, Japan) and a participant information and resource booklet which contains study contact details, weekly step diaries and a physical activity action planning template. The purpose of the pedometer is to allow the participant to set weekly step goals and monitor their own progress in achieving these. The participant familiarises themselves with the function of the pedometer and completes a small walk with the peer mentor to validate the accuracy of the device and ensure they understand how to use it. The meeting concludes with an exchange of contact details and plans to meet the following week.

The initial period of the intervention (activation stage, weeks 1–4) is designed to enable the participant and peer mentor to establish a rapport (e.g. by building a trusting relationship that is necessary for successful peer mentoring).

During this period, the participant will record their baseline levels of physical activity, set early short-term goals and action plan to incorporate additional physical activity into their weekly schedule by agreeing to meet to walk with their mentor (at a minimum of once every two weeks for 45 mins-1 h) and discuss physical activity goals/goal setting and problems/barriers to increasing physical activity with their mentor (weekly face-to-face or over the phone). This period enables the peer mentor to advise the participant of the frequency, intensity, time and type of physical activity they should be taking part in (e.g. by discussing the physical activity guidelines for older adults (copies of which are included in the participant information and resource booklet).

The programme continues (behavioural practice stage, weeks 5–8) with the participant and mentor meeting at least once every 2 weeks to walk and discuss goals/barriers to increasing physical activity. This meeting takes place at a venue of the mentor and participants choosing. This enables the mentor to demonstrate the appropriate walking pace to achieve moderate intensity physical activity and enables the participant to set individual physical activity goals by taking into consideration their capabilities. For the purposes of this study, moderate intensity activity is defined as walking at a pace that leaves the participant slightly breathless but still able to hold a conversation. Weekly activity targets are reviewed and agreed. If the participant is having difficulty increasing their physical activity, the mentor will discuss strategies to overcome barriers to increasing physical activity (e.g. by discussing opportunities for physical activity in the local neighbourhood environment). During this period the mentor and participant begin to plan a walk with a local community based/leisure centre-based walking group (to take place during weeks 10–12) that will facilitate the participant to continue to increase/maintain their activity level when the structured component of the intervention comes to an end.

The final 4 weeks (habit formation stage, weeks 9–12) of the intervention emphasise behaviour rehearsal and practise by walking regularly in a locally accessible physical activity environment (e.g. local park). In order to increase physical activity habit formation, the peer mentor prompts rehearsal and repetition of physical activity behaviour by meeting with/discussing physical activity goals with the participant (e.g. via weekly/biweekly walks/telephone contacts). The final weeks of the structured component of the intervention provide an opportunity for the participant and mentor to discuss other community-based physical activity opportunities and to attend a local community group (e.g. men’s shed) to facilitate the maintenance of physical activity behaviours at the conclusion of the 12-week intervention.

### Peer mentor training

Peer mentors will be recruited concurrently to participant recruitment through partnerships with local community organisations and charitable organisations. Before being appointed as a peer mentor, these individuals will attend a meeting with a member of the research team at a local community venue where they will be provided with information on the study and their role within it. During this session, potential peer mentors will be asked about their willingness to undergo the required training to deliver the programme and their attitude and commitment to helping others increase their physical activity levels. This session will give the mentor an opportunity to discuss their interests, which in turn helps with the process of pairing the peer mentor with a potential participant. Peer mentors will complete approved background checks prior to being matched with potential participants.

Peer mentors will receive training (2 × 1 h standardised training sessions with the project manager using a peer mentor training and support manual) to develop their skill, knowledge and confidence to promote physical activity among their peers. Training is planned to continue during the programme at regular monthly meetings with mentors, such as providing guidance and support during mentoring sessions. During the training sessions, mentors will receive information on important programme responsibilities. These included a peer mentor’s commitment, main tasks and requirements; information about physical activity guidelines for older adults; education about BCTs and their role in the programme; modelling physical activity behaviours; helping their peer complete programme activities; and reporting on activities or providing feedback to the project team. Mentors will be trained on how to build and sustain an effective mentoring relationship with a peer, as well as skills building in the areas of active listening, communication and providing social and emotional support. A full list of the BCTs to be delivered in the intervention is detailed in Table 1.

**Table 1 Tab1:** BCTs in the Walk with me Intervention

Grouping and BCTs (expanded)	Intervention activities
Goals and planning	
Goal setting (behaviour)	Peer mentors will set or agree on a goal defined in terms of the behaviour to be achieved
Action planning	Peer mentors will prompt detailed planning of performance of the behaviour by including specific reference to include (at least one of) context, frequency, duration and intensity of physical activity. Context may be environmental (physical or social) or internal (physical, emotional or cognitive)
Problem-solving	Peer mentors will analyse or prompt the person to analyse factors influencing the behaviour and generate or select strategies that include overcoming barriers and/or increasing facilitators
Review behaviour goals	The peer mentor will review behaviour goal(s) jointly with the person and consider modifying goal(s) or behaviour change strategy in light of achievement
Behavioural contract	Peer mentors will create a written specification of the behaviour to be performed, agreed on by the person and witnessed by another
Feedback and monitoring	
Self-monitoring of behaviour	Peer mentors will distribute pedometers and step diaries to the people that they are mentoring so that they may monitor and record their physical activity behaviour(s) as part of the intervention
Social support	
Social support (practical)	Peer mentors will advise on, arrange or provide practical help for the performance of the behaviour
Social support (emotional)	Peer mentors will advise on, arrange or provide emotional social support for the performance of the behaviour
Shaping knowledge	
Instruction on how to perform the behaviour	Peer mentors will advise or agree on how to perform the behaviour
Natural consequences	
Information about health consequences	The peer mentor will provide information (e.g. written, verbal, visual) about health, consequences of performing the behaviour
Information about social and environmental consequences	The peer mentor will provide information (e.g. written, verbal, visual) about social and environmental consequences of performing the behaviour
Comparison of behaviour	
Demonstration of the behaviour	Peer mentors will provide an observable sample of the performance of the behaviour
Repetition and substitution	
Behavioural rehearsal and practice	Peer mentors will prompt practice or rehearsal of the performance of the behaviour one or more times in a context or at a time when the performance may not be necessary, in order to increase habit and skill
Habit formation	Peer mentors will prompt rehearsal and repetition of the behaviour in the same context repeatedly so that the context elicits the behaviour
Graded tasks	Peer mentors will set easy-to-perform tasks, making them increasingly difficult, but achievable, until behaviour is performed
Antecedents	
Adding objects to the environment	The provision of pedometers will add objects to the environment in order to facilitate performance of the behaviour
Restructuring of the social environment	Peer mentors will change or advise to change the social environment in order to facilitate performance of the behaviour

Peer mentors will also receive a Public Health Agency Information Leaflet ‘Ageing well by being active everyday’ (http://www.publichealth.hscni.net/publications/ageing-well-being-active-every-day) which contains brief information on the physical activity guidelines for older adults and brief advice on how to become more active. Before delivering the programme, outcome measures similar to those collected from participants are recorded including age, sex, physical activity measured with an Actigraph GT3X+ accelerometer, self-rated physical and mental health, social engagement, loneliness, and physical and social activity self-efficacy and outcome expectancy (see below for details).

### Control group

Those assigned to the control group will not receive any additional support to change their activity over the course of the intervention period. They will receive a Public Health Agency Information Leaflet ‘Ageing well by being active everyday’ (the same booklet that will be given to the intervention group). Participants in this group will be informed that after the 6-month data collection point, they will not be offered the opportunity to participate in the intervention; however, they will be given the opportunity to discuss with a member of the project team other community-based physical activity opportunities to facilitate them to change their physical activity behaviour (e.g. information and advice on activity/walking groups that regularly met in that individuals local community/leisure centre).

### Outcome measures

Outcome measures will be assessed at baseline (prior to randomisation), after completing the intervention (12 weeks) and 6 months after baseline (Table 2). All outcomes have been chosen in order to inform the development of a future definitive trial. We plan to assess the feasibility and acceptability of employing these measures.

**Table 2 Tab2:** Outcome measures and time points in the Walk with Me trial

Outcome	Measurement tool	Time points
MVPA	GT3X+ accelerometer	Baseline, 12 weeks, 6 months
Self-reported physical activity	EPAQ-2	Baseline, 12 weeks, 6 months
Physical and mental health	SF-12	Baseline, 12 weeks, 6 months
Mental wellbeing	Warwick-Edinburgh Mental Well-being Scale	Baseline, 12 weeks, 6 months
Health-related quality of life	EuroQol-5D	Baseline, 12 weeks, 6 months
Loneliness	UCLA Loneliness Scale	Baseline, 12 weeks, 6 months
Social engagement	Lubben Social Network Scale	Baseline, 12 weeks, 6 months
Health and social care services resource use	Annotated Cost Questionnaire	Baseline, 12 weeks, 6 months
Acceptability of the intervention	Post-intervention exit questionnaire	6 months
Self-efficacy	Physical Activity Self-Efficacy Measure [49] Social Activity Self-Efficacy Measure (adapted from [49])	Baseline, 12 weeks, 6 months
Outcome expectancies	Physical Activity Outcome Expectancy Measure (Items 1–12 from [50]) Social Activity Outcome Expectancy Measure (Adapted from [50])	Baseline, 12 weeks, 6 months

The primary outcome measure will be mean daily minutes of moderate and vigorous physical activity (MVPA) objectively measured over 7 days using a waist-worn Actigraph GT3X+ accelerometer. Participants will be asked to wear the accelerometer on an elasticated belt, during waking hours, for seven consecutive days. To explore the context of changes in physical activity and the types of physical activity that participants report performing, a validated self-reported physical activity questionnaire (EPAQ-2) [41] will be self-completed.

Informed by the intervention logic model (Fig. 2), secondary outcomes will include physical and mental health and mental wellbeing using the Short-Form 12 (SF-12) Health Questionnaire [42], the 28-item General Health Questionnaire (GHQ-28) [43] and the Warwick-Edinburgh Mental Well-being Scale [44], respectively. Health-related quality of life will be assessed using EuroQol-5D [45]. Social engagement will be measured with the UCLA Loneliness Scale [46] and the Lubben Social Network Scale [47]. Physical activity and social activity self-efficacy [48], and physical activity and social activity outcome expectancies will also be measured [49]).

**Fig. 2 Fig2:**
[figure not shown]
Walk with Me study logic model

Although the trial is not designed to estimate cost-effectiveness, we will pilot the use of participant health and social care services resource use instruments. These will inform the design of the economic evaluation of any subsequent RCT, developed using items from the Annotated Cost Questionnaire [50]. The health and social care services resource use instrument will be given to participants at the outset of the trial, and they will be asked to return it at the 6-month assessment, recording their use of services over that period.

### Process evaluation

In line with MRC guidance on process evaluation [51], we will assess whether the intervention was delivered and received as intended (implementation), how intervention activities, and participants’ interactions with them impacted behaviour change (mechanisms of impact; through behavioural processes as per logic model––Fig. 2); and how potential external factors may have influenced the delivery and functioning of the intervention (context; through post-intervention focus groups).

Process evaluation will assess whether the intervention was delivered and received as intended. This will be achieved through structured observation of intervention delivery (by a member of the research team responsible for mentor training), semi-structured interviews and focus groups with peer mentors and participants, and review of intervention records and participant diaries.

Intervention implementation fidelity will be assessed in the following ways. For each peer mentor, one randomly selected first meeting and follow-up meeting will be audio-recorded and assessed by the research team for content and delivery fidelity, using a quality assurance form.

Feedback on fidelity will be given to each peer mentor during the intervention to assist them in delivery. Completeness in the dose of delivery of the intervention will be assessed by asking the peer mentors and a sample of 10 trial participants to complete weekly checklists and record a diary of contacts (both face-to-face and telephone). The diary will include information on the number of attempts to make contact and the duration of each successful contact. This information will be summarised at the end of the intervention in line with the studies fidelity assessment and implementation plan [52] to assess overall fidelity.

To assess theoretical mediators of physical activity behaviour (mechanisms of impact), physical activity and social activity self-efficacy and physical activity and social activity outcome expectancies will be measured (see study logic model––Fig. 2).

Post-intervention focus groups and semi-structured interviews will be used to provide context to the research by examining how potential external factors may have influenced the delivery and functioning of the intervention.

### Feasibility and acceptability of the intervention

The acceptability of the intervention will be assessed using two approaches. Firstly, all participants will be asked to complete a post-study exit questionnaire, as used in a previous physical activity intervention [53]. This questionnaire asks participants to rate their experience of the intervention and provide reasons for their decision to take part. Other items assess participant satisfaction with the advice/information they received about this study (including the participant information sheet and other information). If the majority of responses are positive, we would assume that the intervention is acceptable; otherwise, we would reflect on how the intervention may be better optimised.

All participants in the intervention group will be invited to attend focus groups or one-to-one semi-structured interviews with an independently appointed researcher to discuss their views on the feasibility and acceptability of the intervention. This will allow us to explore acceptability in greater depth than may have been captured on the exit questionnaire. Focus group/interview participants will be asked to explore reasons for success and challenges to increasing their physical activity and what they would change about the intervention if they were to take part in it again. Participants will not be offered compensation for taking part of the study.

Peer mentors will be invited to attend separate focus groups or one-to-one semi-structured interviews to provide feedback on their experiences of the intervention. Topics will include challenges to intervention delivery, perceived success, and barriers to implementation and suggestions on how to improve the intervention. Primary questions will relate to the different BCTs employed, reviewing each in turn, considering what worked to increase engagement in walking for some individuals and what did not work for others. Control group participants will be invited to attend semi-structured interviews where they can give their feedback on their involvement and their motivation to take part in the research.

Data from the focus groups and interviews will be transcribed verbatim and assessed using content and thematic analysis [36]. These focus groups and interviews will further inform the development and design of a fully powered trial by enabling appropriate refinement of the intervention’s components and delivery for the subsequent RCT, if deemed appropriate. This feedback will also provide an in-depth examination of barriers to and compliance with the implementation of the protocol. The qualitative data thus obtained will help to explain quantitative data regarding recruitment and retention, collected during the process of the intervention, and responses written in the exit satisfaction questionnaire.

The feasibility of conducting a definitive trial, defined as the ability to recruit participants within the time frame, and retain a significant proportion of them within the trial, will be assessed based on the recruitment and attrition rates and the qualitative feedback from participants and mentors. The recruitment rate will be calculated by totalling the number of participants recruited as a proportion of the pre-defined target of 60 participants, within the timeframe of the study. Attrition will be measured as the proportion that does not complete outcome measures at 6 months after baseline (either because they dropped out or failed to complete outcome measures).

#### Assessment of harms

This is a low risk intervention, and we do not anticipate any serious adverse events. However, participants will be encouraged to report adverse events resulting from activity (e.g. musculoskeletal problems, shortness of breath or falls) on an ongoing basis by contacting the study team. Adverse events reported by participants will be recorded on a standard proforma [54].

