### Data analyses

As this is a pilot study, significance tests of change over time will not be performed on the primary of secondary outcomes. Intervention effects will be represented by point estimates, and both 85 and 95% confidence intervals will be estimated at each follow-up time point [55]. Analysis will be conducted by a researcher blind to group allocations. Recruitment, retention and adherence rates will be reported and any adverse events recorded and, alongside effect size, will be used to estimate a sample size required for a definitive trial, if deemed appropriate. All semi-structured interviews and focus groups will be audio-recorded and transcribed verbatim for further analysis. Transcripts from audio recordings will be analysed using standard thematic analysis techniques [36]. At least two qualitative researchers will structure the data and subsequent interpretation. Themes will be compared to the results of the post-study exit questionnaires to make a judgement about the overall acceptability of the intervention.

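### Adverse events are captured only when a participant contacts the team about something they attribute to activity, which risks under-counting in both arms and counts that cannot be read across arms

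*Protocol article*

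**What the plan says.** The section Assessment of harms is the article's only description of how adverse events are found. It says that "participants will be encouraged to report adverse events resulting from activity", with musculoskeletal problems, shortness of breath and falls as examples, and that this happens "on an ongoing basis by contacting the study team". It then says: "Adverse events reported by participants will be recorded on a standard proforma". The rule is addressed to participants in general and does not separate the arms.

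Table 2 (Outcome measures) lists the instruments for baseline, 12 weeks and 6 months. None is an adverse-event item.

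On use of the data, the Data analyses section says: "Recruitment, retention and adherence rates will be reported and any adverse events recorded". The same sentence goes on to the sample size of a definitive trial. It states no comparison of adverse events between arms.

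Contact differs between the arms. In the activation stage (weeks 1–4), intervention participants discuss "problems/barriers to increasing physical activity with their mentor (weekly face-to-face or over the phone"). In weeks 5–8 the pair meets at least fortnightly, and in weeks 9–12 contact is weekly or biweekly. Mentors in turn see the project team: "Training is planned to continue during the programme at regular monthly meetings with mentors". Controls receive a leaflet and otherwise "will not receive any additional support to change their activity over the course of the intervention period".

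**The concern.** Two filters stand between an event and the proforma. The participant must decide that activity caused the event, and must then take the initiative to contact the team. The proforma standardises how a reported event is written down; it does nothing to find events that are not reported.

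The causal filter works least well where it is hardest to apply. A control participant has been assigned no activity, so a fall at home or a sore knee gives little reason to call. An intervention participant with the same event during a programme walk has an obvious cause to name, and has a mentor to talk to. Participants also know their allocation, so their attribution cannot be blind to it.

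The stake is what the pilot hands on. The harms the section itself names are the ones a definitive trial of walking in inactive 60–70-year-olds would need to judge. A low count obtained this way could be taken as confirming the expectation that the intervention is low risk, when it may partly reflect the method of capture.

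**Working it through.** The article gives no adverse-event rate, safety hypothesis or safety sample size, so there is no figure to reproduce. The check has two parts: what the text fixes, and an illustration on assumed rates.

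**What the text fixes**

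- Who starts the report: the participant (Assessment of harms).
- What qualifies: events resulting from activity (same section).
- Scheduled enquiry at shared assessments: none listed (Table 2).
- Arm-specific reporting rule: none.
- Arm-specific contact: mentor contact in the intervention arm (weekly in weeks 1–4, about fortnightly later), no added support in the control arm.
- Planned between-arm comparison of harms: none (Data analyses).

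Under-counting follows directly from the first three lines. Differential capture is an inference from the unequal contact and exposure.

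**Illustration**

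From the article: 60 participants at 1:1, so n = 30 per arm. Assumed: a true risk p of 10% or 20%, equal in both arms, and a capture probability a between 20% and 100%.

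*False reassurance.* The chance that an arm records no affected participant is (1 − p·a)^30. With p = 10%:

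| Capture a | p·a | Chance of none recorded in 30 |
|---|---|---|
| 100% | 0.10 | 0.90^30 = 4% |
| 60% | 0.06 | 0.94^30 = 16% |
| 40% | 0.04 | 0.96^30 = 29% |
| 20% | 0.02 | 0.98^30 = 55% |

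*Under-count.* The expected recorded number is 30·p·a. With p = 20%, the true expectation is 30 × 0.20 = 6.0 per arm. At 60% capture it is 30 × 0.20 × 0.60 = 3.6, and at 40% it is 2.4.

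*If capture differs by arm.* With p = 20% in both arms and 80% capture in the intervention arm (30 × 0.20 × 0.80 = 4.8 recorded):

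- Controls at 60%: 4.8 v 3.6, ratio 1.33, risk difference 0.16 − 0.12 = 0.04. SE = √(0.16×0.84/30 + 0.12×0.88/30) = 0.089.
- Controls at 40%: 4.8 v 2.4, ratio 2.0, risk difference 0.16 − 0.08 = 0.08. SE = √(0.16×0.84/30 + 0.08×0.92/30) = 0.083.

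These ratios are simply the ratios of the assumed capture rates (0.80/0.60 and 0.80/0.40). Swapping the arms inverts them (3.6/4.8 = 0.75 and 2.4/4.8 = 0.5), which is what could happen if intervention participants told their mentor and not the team.

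*With the same enquiry in both arms.* If capture is equal at 60%, the counts are 3.6 v 3.6, with ratio 1 and difference 0.

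**The case against.** The strongest reply is that there is no safety comparison to bias. The Data analyses section only has adverse events recorded, and feasibility is defined by recruitment, retention and qualitative feedback. That stands. A reader might infer that the plan contains a biased between-arm safety comparison, but the article does not support this.

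A reader might also infer that ascertainment is shown to differ by arm, or to inflate the intervention arm. The article does not show this either. It gives one rule and one route for everyone, and it does not say that mentors pass events on. The passage on weekly discussion concerns barriers to activity, covers weeks 1–4 only, and the structured programme ends at 12 weeks. The control-group text withholds support to change activity; it does not rule out contact about adverse events. Differential capture is therefore plausible, with unknown direction.

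The illustrative rates have no source in the article. Both risk differences above are smaller than their standard errors, so 30 per arm would say little about relative harm even with perfect capture. That is a fair limit on the size of the problem, but it does not answer the under-counting.

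Some events may surface elsewhere. The resource-use instrument covers the six months in both arms, and both arms are invited to interviews. The resource-use items are not shown, however, and events without service use would be missed. A fuller protocol or the cited proforma may add prompts or a relatedness item. Even so, the article does more than leave detail out: it states a reporting rule that carries the attribution condition.

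**Conclusion.** The concern holds in a limited form. As written, adverse events are recorded only through participant-initiated contact about events the participant puts down to activity, with no question listed at the shared assessments. This risks under-counting in both arms, and capture may also differ between arms in a direction that cannot be known from the article.

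The consequence is that the recorded counts could falsely reassure. They should not be read across arms, nor carried into planning of the definitive trial as event rates. The wording of the Data analyses sentence is too loose to establish that adverse events feed the sample size itself.

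The size is illustrative only: the 4% to 16–29% range rests on an assumed 10% true risk and 40–60% capture with 30 per arm. For a 60-person pilot this is an inexpensive improvement to harms data; it does not undermine the trial's feasibility aims.

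**What to change.** In Assessment of harms, delete the restriction to events resulting from activity and keep spontaneous reporting. Add one short checklist, asked in the same words of both arms at the existing 12-week and 6-month assessments whatever the suspected cause: falls, musculoskeletal problems, breathlessness, chest symptoms and any hospital attendance. Have the team record relatedness, on the existing proforma if it allows. Add the checklist to Table 2.

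In Data analyses, state that solicited events will be reported by arm descriptively, without a test, and that spontaneous and mentor-relayed reports will be listed separately.

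The cost is one extra page at two assessments that already take place, with no added visits. The recorded event count will be higher, and the report should say that this follows from asking.
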